| ABR      | ABR form, General Assessment and Registration form, is the application form that is required for submission to the accredited Ethics Committee (In Dutch, ABR = Algemene Beoordeling en Registratie) |
| ADL      | Activities of Daily Living                                                                                                                                                                           |
| AE       | Adverse Event                                                                                                                                                                                        |
| APOLLO   | surgical Approach of hemiarthroplasty after femoral neck fracture: POsteroLateral Or direct Lateral                                                                                                  |
| CCMO     | Central Committee on Research Involving Human Subjects; in Dutch: Centrale Commissie Mensgebonden Onderzoek                                                                                          |
| CV       | Curriculum Vitae                                                                                                                                                                                     |
| DHFA     | Dutch Hip Fracture Audit                                                                                                                                                                             |
| DSMB     | Data Safety Monitoring Board                                                                                                                                                                         |
| DLA      | Direct Lateral Approach                                                                                                                                                                              |
| EQ-5D-5L | Health related quality of life                                                                                                                                                                       |
| FES-I    | The Falls Efficacy Scale-International                                                                                                                                                               |
| GEE      | Generalized Estimating Equation                                                                                                                                                                      |
| IC       | Informed Consent                                                                                                                                                                                     |
| ICERs    | Incremental Cost Effectiveness Ratios                                                                                                                                                                |
| ISS      | Injury Severity Score                                                                                                                                                                                |
| KATZ     | Katz Activities of Daily Living                                                                                                                                                                      |
| MCID     | Minimal Clinical Important Difference                                                                                                                                                                |
| MEC-U    | Medical research Ethics Committees United                                                                                                                                                            |
| METC     | Medical research ethics committee (MREC); in Dutch: medisch ethische toetsing commissie (METC)                                                                                                       |
| NE       | Natural Experiment                                                                                                                                                                                   |
| NRS      | Numeric Rating Scale                                                                                                                                                                                 |
| OLVG     | Onze Lieve Vrouwe Gasthuis                                                                                                                                                                           |
| PLA      | Posterolateral Approach                                                                                                                                                                              |
| PIF      | Patient Information Form                                                                                                                                                                             |
| QALY     | Quality Adjusted Life Year                                                                                                                                                                           |
| RCT      | Randomised Controlled Trial                                                                                                                                                                          |
| SAE      | Serious Adverse Event                                                                                                                                                                                |
| SPPB     | Short Physical Performance Battery balance test                                                                                                                                                      |
| SPPS     | Statistical Package for the Social Sciences                                                                                                                                                          |

|                |                                                                                                                                                                                                                                                                                                                                                  |
|----------------|--------------------------------------------------------------------------------------------------------------------------------------------------------------------------------------------------------------------------------------------------------------------------------------------------------------------------------------------------|
| Sponsor | The sponsor is the party that commissions the organisation or performance of the research, for example a pharmaceutical company, academic hospital, scientific organisation or investigator. A party that provides funding for a study but does not commission it is not regarded as the sponsor, but referred to as a subsidising party. |
| Wbp     | Personal Data Protection Act (in Dutch: Wet Bescherming Persoonsgegevens)                                                                                                                                                                                                                                                                 |
| WMO     | Medical Research Involving Human Subjects Act (in Dutch: Wet Medisch-wetenschappelijk Onderzoek met Mensen)                                                                                                                                                                                                                               |

91

92

## SUMMARY

**Rationale:** In the Netherlands the two main surgical approaches for hemiarthroplasty are the posterolateral and the direct lateral approach. Currently there is no conclusive evidence which of these two approaches results in better patient outcomes.

**Objective:** Assessing the patient outcome comparing the posterolateral with the direct lateral approach in patients being treated with cemented hemiarthroplasty after femoral neck fractures.

**Study design:** A randomised controlled multi-center superiority trial and natural experiment with an economic evaluation alongside.

**Study population:** All patients older than 18 years with a femoral neck fracture whereby treatment with cemented hemiarthroplasty is recommended according the national guidelines.

**Intervention:** Treatment with cemented hemiarthroplasty using the posterolateral approach.

**Standard intervention to be compared to:** Treatment with cemented hemiarthroplasty using the direct lateral approach.

**Main study parameters/endpoints:** The primary outcome is the patient-rated quality of life (EQ-5D-5L) at 6 months after surgery.

Secondary outcomes are: ADL functionality (KATZ), Balance test (SPPB), Tendency to Fall (FES-I), Pain (NRS), Re-interventions, Mobility, Discharge destination, Complications, and cost-effectiveness.

**Nature and extent of the burden and risks associated with participation, benefit and group relatedness:** The different approaches in the two treatment arms of the randomised controlled trial are widely used techniques in the Netherlands and many of the outcome measures are part of the standard clinical follow-up after hip fracture. Therefore, there is no extra risk or burden for participating patients, except for the time to complete some additional follow-up measurements. The primary outcome measurement and secondary outcomes, will be assessed through questionnaires online, by hardcopy or by phone at baseline, 3 and 6 months postoperatively. The assessment of the Short Physical Performance Battery (SPPB) balance test, will be performed by one of the study researchers or nurse practitioner to protect continuity and feasibility.

## 1. INTRODUCTION AND RATIONALE

Annually approximately 21.000 patients are admitted to a hospital in the Netherlands with a hip fracture(1). It is the most devastating fracture in the elderly and is associated with excessive utilization of health care resources. The tendency to fall is prominent among elderly and increases with age and frailty level. After a first hip fracture, patients are at increased risk for recurrent falls and prone for additional injuries. This results in impairment of postoperative rehabilitation and increased morbidity and total health-care costs(2). Furthermore, the increased morbidity strongly affects the patients' health related quality of life (HRQoL)(3).

In the treatment of hip fractures, hemiarthroplasty is a commonly used procedure. Different surgical techniques are described in the literature. However, in the Netherlands the two main surgical approaches for hemiarthroplasty are the posterolateral lateral and the direct lateral approach(4).

When inserting a hemiarthroplasty through the posterolateral approach (PLA), the surgeon performs a posterior capsulotomy. During the PLA the hip abductors are protected and preserved preventing limping. However, due to inadequate posterior capsule support there is an increased risk of dislocations(5–10). The direct lateral approach (DLA) involves an incision of the gluteus medius and vastus lateralis muscles. This frequently leads to abductor insufficiency resulting in limping after surgery(11,12). However, in the DLA the posterior capsule is preserved preventing dislocation.

Currently there is no conclusive evidence of which of these two approaches results in the better patient outcomes. The PLA is assumed to be beneficial regarding HRQoL and some studies report that patients operated with PLA are more satisfied and experience less pain after a hemiarthroplasty (13–15). The presumably faster rehabilitation and better balance due to the scatheless gluteus musculature in patients treated using the PLA may be counterbalanced by the increased risk of dislocation. On the contrary, the loss of abductor muscle strength after hemiarthroplasty through the DLA can hypothetically lead to a loss of balance which intensifies the risk of falling and can result in less mobile patients. The increased immobility in the already vulnerable elderly patients will lead to higher risk of falling, asks more of caregivers and patients will rely more on home care facilities.

Hip fracture patients can become more vulnerable and less dependent after subsequent falls. There is still much to gain in terms of reducing these risk factors. Therefore, to detect the differences in surgical approach and improve the patient outcomes is paramount. Well conducted clinical trials comparing the two different – most frequently used in the Netherlands - surgical approaches are absent. Therefore, it remains unknown whether hip fracture patients should be treated using the PLA or the DLA for a cemented hemiarthroplasty.

## HEALTH CARE EFFICIENCY PROBLEM

Currently the Dutch national guidelines recommend either the anterior or the anterolateral approach, despite the lack of high quality evidence. The anterior approach gained popularity – without high level supporting evidence - in elective total hip arthroplasty for osteoarthritis. However, the anterior approach is only used in 3 percent of all hemiarthroplasties in the acute setting, whereas the PLA and DLA are used in respectively 50% and 35% in the treatment of hip fractures with hemiarthroplasty(4). This illustrates the excessively high variance in practice between surgeons and need for high quality evidence. Moreover, as stated above there is an absence of evidence which surgical approach is most beneficial for the patient outcome. Despite the slightly higher risk of dislocation there is a trend to better patient reported outcomes after hemiarthroplasty using the PLA in terms of satisfaction, pain and HRQoL compared with the DLA group(13–15). Thereby, the loss of gluteal muscle strength results in less stability, more limping and can hypothetically lead to a higher tendency to fall which is related with additionally injuries and a prolonged rehabilitation(2). All the more rehabilitation remains the main cost determinant after inserting a hemiarthroplasty(16). The existing knowledge gap which surgical approach is preferable for the patient outcome and the present lack of continuity, gives us a window of opportunity to improve the quality of life and health care for patients with hip fractures treated with a hemiarthroplasty.

## 2. OBJECTIVES

### Primary Objective:

- Does hemiarthroplasty using the posterolateral approach result in a superior patient-reported quality of life compared to the direct lateral approach in the treatment of femoral neck fractures?

### Secondary Objectives:

- Does a hemiarthroplasty using the posterolateral approach lead to a reduction in health care related costs compared to the direct lateral surgical approach?
- Does a hemiarthroplasty using the posterolateral approach lead to better patient outcomes regarding: ADL functionality, balance, tendency to fall, pain, mobility, the number of re-interventions or complications and the discharge destination.

### 3. STUDY DESIGN

A randomised controlled multicenter superiority trial and natural experiment with an economic evaluation alongside. This study will be conducted in the Netherlands and aims for completion within 36 months.

### 4. STUDY POPULATION

#### 4.1 Population (base)

The population base includes all consecutive patients of both sexes and all ethnicities with fractures of the proximal femur admitted to the emergency room or surgery/orthopaedic department of the participating hospitals in the Netherlands during the inclusion period (estimated December 2017 - September 2020).

#### 4.2 Inclusion criteria

In order to be eligible to participate in this study, a subject must meet all of the following criteria:

- $\geq 18$  years at time of trauma
- Acute hip fracture
- Hemiarthroplasty as recommended treatment according the national guidelines
- Dutch or English fluency and literacy
- Informed consent or by proxy in patients with mental impairment

#### 4.3 Exclusion criteria

A potential subject who meets any of the following criteria will be excluded from participation in this study:

- Multi-trauma-patient (ISS > 15)
- Secondary surgery after failed internal fixation
- Patients with a known metastatic disease and a confirmed pathological fracture of the hip
- Fracture > 7 days at time of surgery
- High risk of non-compliance/adherence to study procedures (e.g. no Dutch residency during follow-up period, or other factors that impair follow-up data collection)

#### 4.4 Sample size calculation

We based our sample size calculation on a superiority design. As stated before the EQ-5D will serve as primary outcome measure. We have used the results from earlier studies on this subject for our sample size calculation(17–19). For the sample size calculation, we hypothesized that the EQ-5D will be higher in the PLA group. Using a two-sided significance level ( $\alpha$ ) of 0.05 and a power ( $\beta$ ) of 80% with a standard deviation (SD) of 0.3 and a minimal clinical important difference (MCID) of 0.08 (derived from the study mentioned before) a total of 222 subjects are needed in each treatment arm. Taking into account a 25% loss to follow-up after six months, a total number of 610 participants are needed in this superiority design.

## 5. TREATMENT OF SUBJECTS

### 5.1 Investigational treatment

Patients allocated to the PLA group will receive a cemented hemiarthroplasty using the PLA.

#### *Technique classic PLA*

Patient in side position. Exposure is made through a 10-15 cm curved incision that begins about 7 cm cranial and posterior of the greater trochanter and continue across the greater trochanter down towards the femur shaft. In line with the skin incision, the fascia lata is incised to exposure the distal vastus lateralis. The gluteus maximus muscle is separated by blunt dissection. Stretch the short external rotators and detach the piriformis and obturator internus muscle. Expose the hip joint by a longitudinally incision of the posterior capsule. Dislocate the hip with internal rotation after capsulotomy.(20)

[figure not shown]

The type and brand of the prosthesis will be left to the surgeons' discretion. Hospital protocols and guidelines will be followed regarding physical therapy and rehabilitation program and will be recorded.

Patients allocated to the DLA group will be treated with a cemented hemiarthroplasty using the DLA.

#### *Technique classic DLA*

Patient in supine position. Exposure is made through a longitudinal incision beginning about 5 cm proximal and continuing over the tip of the greater trochanter and extends down the line of the femur shaft for 8 cm. Incise fascia lata in line with the skin incision. Retract the fascia lata anteriorly and the gluteus maximus posteriorly. Blunt dissection of any fibers of gluteus medius that attach to fascia lata. Insertion of the gluteus medius through a crescent shaped course 3-5 cm above the greater

[figure not shown]

trochanter and extend the incision inferior through the fibers of vastus lateralis. Develop an anterior flap by sharp dissection of anterior gluteus medius fibers and the anterior part of the vastus laterals of the bone. Exposure of the hip joint is reached by releasing the gluteus minimus from the anterior greater trochanter to expose and dissect the anterior joint capsule.(21)

The type and brand of the prosthesis will be left to the surgeons' discretion and implant specifications will be recorded. Physical therapy and rehabilitation will be administered following the standard protocols and guidelines from the center of inclusion.

## **6. METHODS**

### **6.1 Study parameters/endpoints**

#### **6.1.1 Main study parameter/endpoint**

The primary outcome is the patient (or proxy)-rated quality of life (EQ-5D-5L) at 6 months after surgery.

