## 6.4 Study procedures

|                              | Screening                              | Informed consent procedure       | Baseline assessment | Surgery                                               | 4 weeks follow up              | 3 months follow up                                                              | 6 months follow up                                                              |
|------------------------------|-----------------------------------------------|-----------------------------------------|----------------------------|--------------------------------------------------------------|---------------------------------------|----------------------------------------------------------------------------------------|----------------------------------------------------------------------------------------|
| Clinician/ researcher | Identify eligible patients with hip fractures | Explain PIF, answer questions, sign ICF | DHFA*                      | Record implant details
Record complications               |                                       | Standard clinical follow up, including DHFA                                            | Standard clinical follow up                                                            |
| Researcher            | Identify eligible patients with hip fractures | Answer additional questions if needed   | - DHFA
- EQ-5D          | Screen surgical report for relevant information if necessary | Health care utilization questionnaire | - EQ-5D
- FES-1 scale
- NRS
- SPPB
- Health care utilization questionnaire | - EQ-5D
- FES-1 scale
- NRS
- DHFA
- Health care utilization questionnaire |
| Patient/ proxy        |                                               | Read PIF, ask questions, sign IC        | Complete questionnaire     |                                                              | Complete questionnaire                | - Complete questionnaires
- SPPB at outpatient clinic                               | Complete questionnaires                                                                |

\*DHFA is a registry used in standard care includes: living status, pre-mobility score, KATZ, ASA, complications, discharge destination, re-operations

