When hospitals are participating with this trial, treating physicians will be asked to screen if patients admitted to the hospital with a hip fracture are eligible for study entry. If inclusion criteria are met, they can contact the research coordinator by phone (☎ ([contact]) or visit the trial website, for further assistance with obtaining informed consent, randomisation and inclusion of the patient.

To obtain informed consent, the patient information letter will be handed out to eligible patients or to their health care proxy. Hard copies will be available in all participating hospitals or could be found as a download on the trials' website.

Hip fractures are injuries where treatment is required in less than 48 hours for optimal outcomes. Therefore, the time in which patients can consider if they are willing to participate to the study, is limited to the time until surgery. Informed consent of patients in the Natural Experiment can be obtained after surgery. The research coordinator will contact these patients.

For patients with severe cognitive impairment due to dementia, informed consent will be obtained by their health care proxy. It is to the doctors' opinion to determine if a patient

has a cognitive impairment. When the diagnosis is not clear, a clinical geriatric doctor will be consulted

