### **Baseline assessment**

At baseline we will assess the EQ-5D-5L, the ADL functionality (KATZ), pre-mobility score and the living status using the Dutch Hip Fracture Audit (DHFA) registration. The assessment of the above outcomes is based on the health status prior to the trauma.

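### The objective and Summary name the patient's own rating, the endpoint also accepts a proxy's, and no rule fixes or records who rates the EQ-5D-5L

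*Protocol*

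**What the plan says.** Three places in the protocol describe the primary outcome:

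- Section 2, primary objective: whether the posterolateral approach would "result in a superior patient-reported quality of life compared to the direct lateral approach".
- Summary: "The primary outcome is the patient-rated quality of life (EQ-5D-5L) at 6 months after surgery".
- Section 6.1.1: "The primary outcome is the patient (or proxy)-rated quality of life (EQ-5D-5L) at 6 months after surgery".

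The schedule in section 6.4 has a single row labelled "Patient/ proxy", with the entry "Complete questionnaire" at baseline and matching entries at later visits. The EQ-5D is collected at baseline, 3 and 6 months, by web form, paper or telephone. The baseline rating is retrospective: "The assessment of the above outcomes is based on the health status prior to the trauma".

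Elsewhere a proxy is discussed only as the person who consents. Section 4.2 lists "Informed consent or by proxy in patients with mental impairment". Section 6.4 says "For patients with severe cognitive impairment due to dementia, informed consent will be obtained by their health care proxy", and leaves the judgement of impairment to the doctor, with a geriatrician consulted if it is unclear. Sections 9.2 and 9.3 refer to cognitive impairment, with dementia as an example.

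Section 8.1 specifies a GEE model with EQ-5D as the dependent variable and arm, time and their interaction as terms. Section 8.2 plans a subgroup analysis in patients with dementia.

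**The concern.** A patient's own rating and another person's rating of that patient are two different measurements. The objective asks about the first, while the endpoint definition admits both under one name. A reader of the final result would not know which question it answers.

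The protocol also leaves open three matters that are settled when data are collected: which patients a proxy rates, whether the same person rates from baseline to 6 months, and whether the form shows who answered. On a web or paper form, the research team may not see who filled it in.

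The trial deliberately enrols frail and cognitively impaired patients, so a material number of proxy ratings is to be expected. Whether a patient needs a proxy at 6 months can depend on recovery, and the surgical approach is hypothesised to affect recovery. Section 6.2 says the trial is unblinded, and allocation in the natural experiment of section 6.3 is not randomised. If proxy use after surgery came to differ by approach, part of the estimated effect would be a difference in raters.

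**Working it through.** **1. The passages side by side.** The Summary and section 2 mean the patient. Section 6.1.1 means the patient or a proxy. The consent provisions name a group of impaired patients but do not say that this group, and only this group, is rated by proxy. No section permits the rater to change between visits and none prevents it. No section provides for recording the rater.

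**2. The plan's own figure.** Section 4.4 gives SD 0.3, difference 0.08, two-sided alpha 0.05 and power 80%. Then n per arm = 2 × (1.960 + 0.842)² × 0.3² / 0.08² ≈ 221 by the normal approximation, and 222 by the two-sample t-test. The stated 222 is reproduced, so 0.08 is the right yardstick for what follows.

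**3. How the rater enters the contrast.** Let d be the proxy-minus-self gap on the EQ-5D index, and let p be the share of proxy ratings in an arm at a visit. The observed mean is the mean on the self-rated scale plus d × p. From baseline to 6 months the group-by-time contrast therefore contains an extra term:

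shift = d × [(change in p, posterolateral arm) − (change in p, direct lateral arm)]

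- Rater never changes: shift = 0, whatever the share of proxies.
- Proxy share rises by 10 points in both arms: shift = d × (0.10 − 0.10) = 0. The rise appears in the time effect only.
- Proxy share rises by 10 points more in one arm, with d = 0.10: shift = 0.10 × 0.10 = 0.01, and 0.01 / 0.08 = 12.5%.

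The protocol gives neither d nor the proxy shares. Over an assumed range, in either direction:

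| Imbalance in change of proxy share | d = 0.05 | d = 0.10 | d = 0.15 | d = 0.20 |
|---|---|---|---|---|
| 5 points | 0.0025 (3.1%) | 0.005 (6.3%) | 0.0075 (9.4%) | 0.01 (12.5%) |
| 10 points | 0.005 (6.3%) | 0.01 (12.5%) | 0.015 (18.8%) | 0.02 (25%) |

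Percentages are of 0.08.

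**4. Cost of pooling in precision.** If 0.3 is the SD within one type of rater, the pooled SD is √(0.3² + p(1 − p)d²).

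- p = 0.3, d = 0.10: √(0.09 + 0.0021) = 0.3035; 226 per arm needed; power at 222 per arm 79.3%.
- p = 0.4, d = 0.15: √(0.09 + 0.0054) = 0.3089; 234 per arm needed; power at 222 per arm 77.9%.

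Against 80.2% at 222 per arm with SD 0.3, the loss is at most about 2 percentage points. It is smaller still if the 0.3 already reflects mixed raters.

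**The case against.** The strongest reply is that the protocol never says the rater may change. The row in the schedule also covers reading the information form and signing consent, so it may simply list whoever acts for the participant. Proxies otherwise appear only for impaired patients, who are identified at consent, and the natural reading is that the same patients are proxy-rated throughout. This stands as far as it goes. A reader might infer that the protocol lets raters switch, but that is an inference from silence. What remains is that the protocol does not state the natural reading, and it describes the impaired group in different terms in different sections.

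Second, randomisation balances the proxy share at baseline in expectation, equal switching cancels, and nothing in the protocol shows that switching would differ by approach. This stands. Section 6.3 also says patients will be blinded to the hypothesis, which tempers the argument from open treatment, and the protocol does not say that proxies know the approach.

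Third, a rater term or sensitivity analysis may be in the statistical analysis plan. That is possible, but such an analysis needs the rater to have been recorded, and that cannot be repaired afterwards.

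Fourth, the dementia subgroup partly separates the raters. It does so only in part: it is defined by diagnosis, so a patient without dementia who needs a proxy after surgery stays unmarked in the main analysis.

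**Conclusion.** The inconsistency is on the page: the objective and Summary describe one measurement and section 6.1.1 another. No rule says when a proxy rates, keeps the rater constant or records who answered. This should be corrected, and it is not a fatal flaw.

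The effect on the treatment comparison is conditional. It is zero if proxy use changes equally in both arms. With a 5- to 10-point imbalance and a gap of 0.05 to 0.20 it is 0.0025 to 0.02, or 3% to 25% of 0.08, and the upper end takes both assumptions at their extreme. All these inputs are assumptions, and no direction can be given.

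Three stronger readings are not supported:

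- A reader might conclude that the primary result is biased. The protocol does not show differential proxy use.
- A reader might conclude that proxies should not be used, or that pain (NRS) and FES-I should be restricted to self-report. In a trial that sets out to include impaired patients that is a trade-off, not a correction.
- A reader might compare the false change in one patient who switches rater with 0.08. That figure is a difference between group means, so the two quantities are not comparable.

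**What to change.** 1. Align the Summary, section 2 and section 6.1.1 on one description: *EQ-5D-5L rated by the patient, or by a proxy where the patient cannot answer*.
2. Designate the rater at baseline from the cognitive judgement already made for consent, and keep the same rater at every visit where possible. Consent in the natural experiment can follow surgery, so there the designation should rest on cognitive status before the operation.
3. Record on every form who actually answered. Without this, no later analysis can examine the question.
4. Include baseline rater status (self or proxy) as a covariate in the primary model, with all patients kept in. This handles differences between patients; it does not correct a switch after baseline, which is why item 3 is needed.
5. Add a supportive analysis in patients designated self-raters at baseline. The group is fixed before surgery, so it does not select on recovery, as an analysis of whoever self-rates at 6 months would.
6. Keep proxy answers for NRS and FES-I; at most, report those outcomes by rater.

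The cost is one form field, one rule for the research coordinator and a little more analysis. No patient is excluded and the sample size does not change.
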